### Intervention completion and withdrawal

Study completion is defined as 12 months after the date of randomisation. There are three withdrawal options available to participants:

Withdrawal from the OptiCALS intervention only, that is, no further intervention delivery visits but the participant remains in the trial. The participant and/or clinician can make the decision to discontinue the intervention for any reason.Withdrawal from the OptiCALS trial, but with consent for the collection of essential routine data from hospital notes, that is, survival status/cause of death and ALSFRS scores, where available. No further intervention or research visits will be conducted with the participant.Withdrawal from the OptiCALS trial entirely, with no consent given to collect essential routine data. Unless specified by the participant, all data collected up to this point will be used in the analysis and no further intervention or research visits will be conducted.

Where participants have withdrawn, but consent to routine clinical data being collected, ALSFRS-R will be collected from their medical records along with survival status.

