### Sample size

The sample size was derived by simulation with parameters estimated from the PRO-ACT ALS clinical trials data repository.^45^ The ALSFRS-R at entry was assumed to have a mean (SD) of 37 (6) and a mean monthly decline of 1 unit over the 12-month duration of follow-up, with successive values following with an autoregressive (AR1) correlation structure with rho=0.9. A difference of +0.25 units per month (ie, a monthly decline of 0.75 in the intervention arm vs 1.00 in the control arm) was taken as a clinically meaningful effect. The probability of death was assumed to depend on the last known ALSFRS-R with the probability of death in each 3-month period assumed to be zero up to month 3 and then as 91*exp[−0.115*(ALSFRS-R at previous visit)−3.95] thereafter, equating to an 18% death rate for the control group and 15% in the intervention at 12 months. These parameters were based on fitting a Cox regression model for survival in which ALSFRS-R score was a time-dependent covariate. Participants who die are included in the analysis and allocated a functional score of zero. Withdrawal was assumed to occur at a rate of 5% per quarter in both groups, again starting after the month 3 visit. With a two-sided alpha of 5%, a power of 85% and with the first 100 participants allocated in a 1:1 ratio and the remaining participants allocated 1:2 (standard care vs OptiCALS intervention), this requires a sample size of 103 in the standard care arm and 156 in the OptiCALS intervention arm, n=259 participants in total.

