## Data analysis

### Primary outcome

The primary outcome ALSFRS-R will be analysed longitudinally using a multilevel linear mixed effect model estimated by restricted maximum likelihood. The fixed effect covariates will be time, treatment and their interaction together with variables used in the minimisation process. The recruitment centre will be incorporated as a random intercept in which participants are nested within their centre. If this model fails to converge, the centre effect will be removed and the simpler model will be fitted. The area between the two ALSFRS-R curves will be derived using a linear combination of the coefficients for treatment and the interaction of treatment with time and will be presented alongside its 95% CI and p value. The difference in ALSFRS-R will also be quantified separately at each timepoint.

The primary analysis will be intention-to-treat and will include all patients for whom data are collected or who have died; an ALSFRS-R functionality score will be assigned for all timepoints scheduled after the date of death. Sensitivity analyses will be performed to assess the robustness of the findings to distributional assumptions, baseline characteristics and imbalance, missing data and non-adherence.^46^

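### For participants who withdraw but allow use of routine data, a death always enters the primary analysis as zeros while a living score enters only if the notes hold one; this biases the comparison if withdrawal is unequal and notes are incomplete

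*Protocol article*

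**What the plan says.** The protocol article (Intervention completion and withdrawal) gives three options.

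- **Option 1** stops the intervention only. The participant stays in follow-up.
- **Option 2** ends all trial visits but keeps consent for routine data from hospital notes: "survival status/cause of death and ALSFRS scores, where available". The section's closing sentence says that ALSFRS-R will be taken from the medical records together with survival status.
- **Option 3** ends all collection, routine data included.

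Under Data analysis, Primary outcome, the intention-to-treat analysis "will include all patients for whom data are collected or who have died; an ALSFRS-R functionality score will be assigned for all timepoints"; the sentence goes on to limit this to visits due once the participant has died. That section does not give the value; Sample size does: "Participants who die are included in the analysis and allocated a functional score of zero". The model is a linear mixed model with time, treatment and their interaction, and the estimate is the area between the two curves. Missing data appear there only in a list of sensitivity analyses, without detail. Study outcomes adds a check of survival status at the end of the study. Sample size assumes the same withdrawal, 5% per quarter, in both arms.

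**The concern.** Take two option-2 participants with the same history. One dies and contributes a zero at every later visit. The other lives and contributes only if a clinic recorded an ALSFRS-R that can be matched to a visit. Whether a value is seen then depends on the value itself, even if the decision to withdraw was random. A mixed model fitted to observed data assumes the opposite. It fills in for the unseen living participants from visit means that carry too many zeros.

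Each arm is pulled down according to its own withdrawal. If the arms withdraw equally, the pull cancels in the comparison. If they do not, the arm with more withdrawal looks worse. Participants know their allocation, and only the intervention arm has the calorie-target visits and follow-up calls, so equal withdrawal cannot be taken for granted. A real benefit could be partly hidden or, if controls withdraw more, exaggerated.

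**Working it through.** **Inputs (Protocol article, Sample size).** Entry mean 37, SD 6; "autoregressive (AR1) correlation structure with rho=0.9"; decline of 1.00 v 0.75 per month; quarterly death probability after month 3 of 91*exp[-0.115*(previous score) - 3.95]; zero after death; withdrawal after month 3; "103 in the standard care arm and 156 in the OptiCALS intervention arm".

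**Assumed, because the article gives no figure.** Unequal withdrawal rates, the share of withdrawals under option 2, and the share of living option-2 participants with a usable score in the notes. Withdrawal was simulated as unrelated to prognosis.

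**Reproducing the plan.** Simulated 12-month deaths are 17.9% and 15.0% (stated 18% and 15%). Power for the treatment-by-time term is 82-83% (stated 85%; the article does not say which model its simulation fitted).

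**Planned effect on the two scales.** Month 12: 0.25 x 12 = 3 points. Area: 0.25 x 12^2 / 2 = 18 point-months, and 18 / 12 = 1.5 points on the 12-month average.

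**Hand check.** Let d be the proportion dead and W = 1 - (1 - w)^3 the cumulative withdrawal over three quarters at rate w. If no living withdrawn participant has a score, the dead share of observed data at month 12 is d / [d + (1 - d)(1 - W)]. With d = 0.18:

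- w = 5%: W = 0.143, share 0.18 / (0.18 + 0.82 x 0.857) = 20.4%
- w = 10%: W = 0.271, share 23.1%
- w = 15%: W = 0.386, share 26.3%

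The simulated complete-data control mean is 21.09 with 17.9% dead, so survivors average 21.09 / 0.821 = 25.7. Observed means are then 25.7 x (1 - 0.204) = 20.5 at 5% and 25.7 x (1 - 0.231) = 19.8 at 10%. That is a raw gap of about -0.7 between two arms with no true difference. The mixed model recovers part of it from earlier scores, leaving about -0.45.

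**Bias under no treatment effect** (random participant intercept, linear time; control v intervention; a dash means not reported):

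| Withdrawal per quarter | Share under option 2 | Living scores found | 12-month average | Month 12 |
|---|---|---|---|---|
| 5% v 5% | all | none | 0.00 | about 0 |
| 5% v 7.5% | all | none | -0.09 | -0.2 |
| 5% v 10% | all | none | -0.19 | -0.45 |
| 2.5% v 10% | all | none | -0.27 | -0.64 |
| 5% v 15% | all | none | -0.4 | -0.9 |
| 10% v 5% | all | none | - | +0.4 |
| 5% v 10% | all | half | - | about -0.2 |
| 5% v 15% | all | half | - | about -0.3 |
| 5% v 10% | half | half | -0.05 | -0.12 |

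With all living scores found, or with nothing scored after withdrawal in either arm, the month-12 bias is within about 0.1 of zero.

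**Dependence on the model.** Categorical time with unstructured covariance gives about the same month-12 bias (-0.4 at 5% v 10%, -0.9 at 5% v 15%). Linear time with unstructured covariance gives only -0.06 at 5% v 10%.

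**Under the planned effect, all option 2 and no living scores.** The estimated slope difference falls from 0.27 at equal 5% withdrawal to 0.23 (5% v 10%) and 0.18 (5% v 15%). Power for the slope falls from 83% to 70% and 56%. With nothing scored after withdrawal it would be 82% and 79%, so most of the loss comes from the scoring asymmetry and not from withdrawal itself.

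**The remedy.** Imputing living withdrawn participants by arm from earlier scores, then assigning zero to the dead, left a bias of 0.01 or less in every case tried with all withdrawals under option 2 and no living scores.

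**The case against.** The article intends to collect ALSFRS-R from the notes of these participants, not just survival, and the where-available qualifier can be read as covering both. If the notes are complete, there is no bias. A participant tired of intervention contacts can choose option 1 and stay in follow-up. Controls keep food diaries too, reduced data collection is offered, and ALSFRS-R can be self-completed by post or email. All of this makes a large imbalance under option 2 less likely.

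The 12-month average is the scale closest to the planned area between curves. Its standard error is about 0.92, so a bias of -0.05 is about a twentieth of a standard error. If the intervention arm withdraws more, the error is conservative for a superiority claim. Missing-data sensitivity analyses are promised, and their detail may stand in an analysis plan that is not shown.

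These points stand as limits on scope and size. They do not remove the asymmetry. Routine notes need not hold a score near each scheduled visit, and the article fixes the primary data set and scoring rule itself. A sensitivity analysis would leave the primary estimate unchanged.

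A reader might infer that deaths are captured after every withdrawal, that living scores will mostly be missing, or that the primary result will be biased. The article supports none of these. Option 1 loses no data, option 3 gives no consent to collect deaths or scores, and neither the completeness of notes nor unequal withdrawal is documented.

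**Conclusion.** The defect is real but conditional. It concerns option 2 only, and it needs both unequal withdrawal between arms and incomplete notes. The bias then runs against the arm with more withdrawal.

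Under the least favourable assumptions, for 5% v 7.5-15% per quarter, it is about 0.1 to 0.4 points on the 12-month average and 0.2 to 0.9 at month 12. That is roughly 6% to 27% of the planned 1.5 points (0.09 / 1.5 and 0.4 / 1.5). In the milder case of 5% v 10% with both shares at one half, it is about 3% (0.05 / 1.5). The rates, the option-2 share and the availability of scores are all assumed. The size also depends on the covariance model, which the article does not specify, and withdrawal related to prognosis could change it. The point is worth correcting because it touches the primary estimate and costs little to remove.

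**What to change.** In the primary analysis, treat dead and living option-2 participants alike:

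1. Multiply impute missing ALSFRS-R at each visit for participants known to be alive then. Impute by arm, using living participants only, from their earlier scores and any score from the notes.
2. Assign zero at visits after death, and state that value in the analysis section.
3. Fit the planned model to each completed data set and combine the results.

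Treat option-3 participants as missing after withdrawal, and impute their vital status only in a sensitivity analysis. Report, by arm, the numbers under each withdrawal option and the proportion of scheduled visits for which a notes-based score was found.

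The cost is a change of wording and a standard imputation step, with no new data. Confidence intervals may widen slightly. Imputation rests on its own assumption, that withdrawn living participants resemble other living participants with the same history.

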### Uptake of intervention

The intervention comprises several components (see table 1), each of which can be measured by the number of times accessed and the time span over which patients continue to engage with it. Each component will be summarised individually, and visual displays will depict how each individual engages with each component across time. For purposes of the analysis, these will be used to provide an overall assessment (blind to outcome) of whether each participant had engaged sufficiently to be considered ‘compliant’ with the intervention.

### Sample size

The sample size was derived by simulation with parameters estimated from the PRO-ACT ALS clinical trials data repository.^45^ The ALSFRS-R at entry was assumed to have a mean (SD) of 37 (6) and a mean monthly decline of 1 unit over the 12-month duration of follow-up, with successive values following with an autoregressive (AR1) correlation structure with rho=0.9. A difference of +0.25 units per month (ie, a monthly decline of 0.75 in the intervention arm vs 1.00 in the control arm) was taken as a clinically meaningful effect. The probability of death was assumed to depend on the last known ALSFRS-R with the probability of death in each 3-month period assumed to be zero up to month 3 and then as 91*exp[−0.115*(ALSFRS-R at previous visit)−3.95] thereafter, equating to an 18% death rate for the control group and 15% in the intervention at 12 months. These parameters were based on fitting a Cox regression model for survival in which ALSFRS-R score was a time-dependent covariate. Participants who die are included in the analysis and allocated a functional score of zero. Withdrawal was assumed to occur at a rate of 5% per quarter in both groups, again starting after the month 3 visit. With a two-sided alpha of 5%, a power of 85% and with the first 100 participants allocated in a 1:1 ratio and the remaining participants allocated 1:2 (standard care vs OptiCALS intervention), this requires a sample size of 103 in the standard care arm and 156 in the OptiCALS intervention arm, n=259 participants in total.

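### The 85% power is not shown for the primary test: on the stated inputs, the area between the curves falls short of it under every reading checked that scores deaths as zero

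*Protocol article*

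**What the plan says.** The Sample size section of the protocol article says the number was derived by simulation. Its inputs are:

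- **Level and course:** "The ALSFRS-R at entry was assumed to have a mean (SD) of 37 (6) and a mean monthly decline of 1 unit".
- **Correlation:** "successive values following with an autoregressive (AR1) correlation structure with rho=0.9".
- **Effect:** "a monthly decline of 0.75 in the intervention arm vs 1.00 in the control arm".
- **Deaths:** none up to month 3, then a quarterly probability of "91*exp[−0.115*(ALSFRS-R at previous visit)−3.95] thereafter, equating to an 18% death rate for the control group and 15% in the intervention at 12 months".
- **Score after death:** "Participants who die are included in the analysis and allocated a functional score of zero".
- **Withdrawal:** 5% per quarter in both arms, after month 3.
- **Error rates and early allocation:** "With a two-sided alpha of 5%, a power of 85% and with the first 100 participants allocated in a 1:1 ratio"; later participants are split 1:2.

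The result is that "this requires a sample size of 103 in the standard care arm and 156 in the OptiCALS intervention arm, n=259 participants in total". The section does not say which coefficient or contrast was tested in the simulated trials.

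Under Data analysis, Primary outcome, the model contains time, treatment, their interaction and the minimisation variables, with centre as a random intercept. The reported result is then defined: "The area between the two ALSFRS-R curves will be derived using a linear combination of the coefficients for treatment and the interaction". It is given with its 95% CI and p value. No other contrast in that section is said to carry a p value. The Randomisation section lists the minimisation factors as site, ALSFRS-R trajectory since symptom onset, and riluzole use. Baseline ALSFRS-R itself is not listed as a covariate.

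**The concern.** The power section speaks of a slope, and the analysis section tests an area. The two contrasts have different precision. The area includes the treatment main effect, and so carries the between-participant spread at entry unless baseline is adjusted for. Scoring deaths as zero adds further variance. A power figure for one contrast cannot be carried over to the other.

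At stake is how the result is read. A null finding from a test thought to have 85% power is taken to miss the target effect 15% of the time. If the true power is 35–50%, the miss rate is 50–65%; if it is 54–74%, the miss rate is 26–46%.

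**Working it through.** **1. Reproduce the inputs.** Allocation: 50 + 53 = 103 and 50 + 106 = 156 (159 remaining participants split 1:2). Simulated 12-month deaths are 17.8% and 14.9%, against the stated 18% and 15%. The data-generating model is therefore read as intended.

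**2. Define the contrast.** With linear time in months, area = 12·b(treatment) + 72·b(interaction). Under the target effect this is 72 × 0.25 = 18, an average difference of 18/12 = 1.5 units.

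**3. Hand check, no deaths or withdrawal.** Take visits at 0, 3, 6, 9 and 12 months, with trapezoid weights 0.125, 0.25, 0.25, 0.25 and 0.125, and AR1 0.9 per visit. The variance factor is 0.21875 + 2(0.9×0.1875 + 0.81×0.125 + 0.729×0.0625 + 0.6561×0.015625) = 0.870.

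- SD = 6 × √0.870 = 5.60
- SE = 5.60 × √(1/103 + 1/156) = 0.711
- z = 1.5/0.711 = 2.11; power ≈ Φ(2.11 − 1.96) = 56%

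**4. Score deaths as zero.** The simulated SD of the 12-month average rises to about 7.29 and the mean difference becomes about 1.57.

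- SE = 7.29 × 0.127 = 0.93
- z ≈ 1.57/0.93 = 1.69; power ≈ Φ(−0.27) = 39%

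**5. Full simulation** (103/156, deaths zero, withdrawal as stated, scores limited to 0–48). The main case used 1,500 replicates, so the Monte Carlo SE at 40% is √(0.4×0.6/1500) = 1.3 points. Visit set (with or without month 1), AR1 lag and covariance structure were varied.

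| Area contrast | Power |
|---|---|
| No baseline covariate, quarterly visits, AR1 per visit | 40% (random intercept), 39% (random slope), 39% (AR1 residuals) |
| Same, all variants | roughly 35–50% |
| Trajectory covariate, onset time assumed | about 40–59% |
| Baseline ALSFRS-R adjusted, all variants | about 54–74% |

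Leaving the baseline visit out of the outcome vector, with no baseline covariate, gave 30–39%. Under no effect, the three main-case models in the first row rejected 4–5% of the time.

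**6. The slope test on the same data.**

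| Time-by-treatment test | Power | Type I error |
|---|---|---|
| Unstructured covariance, quarterly visits | 83–84% | about 5.5% |
| Unstructured, month 1 added | 71% | |
| Unstructured, rho per month | 58% | |
| AR1 residuals, quarterly | 69% | 5% |
| Random slope, quarterly | 58% | 4% |
| Random intercept only, quarterly | 83% | 19% |

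Other readings gave 55–65%. The area with the treatment main effect dropped reaches 86% in a random-intercept-only model, but rejects 23% of the time under no effect.

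**The case against.** The strongest reply is that nothing has been miscalculated. The Sample size section never claims to have simulated the area test. It states the effect as a slope, and a valid slope test can give 83–84% from the stated inputs. On that view the fault is a mismatch between two sections. This stands in part: the documents do not show an arithmetic error, and the origin of the 85% can only be inferred. It does not rescue the figure, because a reader will attach it to the only contrast given a p value.

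Second, a model without any baseline covariate is not quite the planned one. The trajectory factor is among the minimisation variables and presumably draws on the entry score. That is correct, so 35–50% should not be presented as the power of the planned model. With a trajectory term the range is about 40–59%, but it rests on an assumed time since onset; the inclusion criteria give only an upper limit of two and a half years.

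Third, the article defers detail to an SAP, which may add baseline ALSFRS-R. Power then rises, but only to about 54–74%.

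Fourth, the reported CI will show how informative a null result is, whatever power was planned. That softens the consequence but does not correct the statement.

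A reader might also infer that the slope was what the sponsor powered, and that making it the primary contrast would settle the matter. The documents do not say so, and the slope holds near 85% only under one combination of covariance and visits. The Study outcomes section schedules a month 1 visit, which that combination leaves out.

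**Conclusion.** The concern holds as a mismatch between the stated power and the stated primary test. With deaths scored zero, no version of the area contrast examined reaches 85%: roughly 35–50% without a baseline covariate, about 40–59% with a trajectory covariate, and about 54–74% with baseline ALSFRS-R.

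These figures assume SD 6 at every visit (the protocol gives it only at entry), rho 0.9 per visit or per month, linear time and no centre variance. Changing the correlation lag, visit set and covariance moved the numbers but not the conclusion. Deaths left missing would lift baseline-adjusted power to about 80–99%, but that contradicts the stated zero score.

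The material does not support one replacement figure such as 40%. That depends on the covariates, the covariance structure and the sponsor's simulation code, which are not shown.

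**What to change.** Before unblinding:

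- Re-run the simulation with exactly the estimator under Data analysis, Primary outcome: the area contrast, the minimisation covariates, the planned covariance structure and visit set, and zero after death.
- Decide and fix whether baseline ALSFRS-R enters the model, and simulate that model.
- Report power and type I error for that estimator, and put the power for 103/156 in place of 85%.
- Name the powered contrast in the Sample size section, and state the SD after entry and the time unit of rho.

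Keep n at 259 and keep the area as the primary contrast. The cost is one simulation re-run, a few sentences of wording, and a stated power that will look less favourable.

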## Data analysis

### Primary outcome

The primary outcome ALSFRS-R will be analysed longitudinally using a multilevel linear mixed effect model estimated by restricted maximum likelihood. The fixed effect covariates will be time, treatment and their interaction together with variables used in the minimisation process. The recruitment centre will be incorporated as a random intercept in which participants are nested within their centre. If this model fails to converge, the centre effect will be removed and the simpler model will be fitted. The area between the two ALSFRS-R curves will be derived using a linear combination of the coefficients for treatment and the interaction of treatment with time and will be presented alongside its 95% CI and p value. The difference in ALSFRS-R will also be quantified separately at each timepoint.

The primary analysis will be intention-to-treat and will include all patients for whom data are collected or who have died; an ALSFRS-R functionality score will be assigned for all timepoints scheduled after the date of death. Sensitivity analyses will be performed to assess the robustness of the findings to distributional assumptions, baseline characteristics and imbalance, missing data and non-adherence.^46^

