### Randomisation

Participants will be allocated to one of two groups: standard treatment; standard treatment plus OptiCALS intervention (originally in a 1:1 ratio, amended during the study to a 1:2 ratio). Randomisation is via a web-based randomisation system, employing non-deterministic minimisation by including a random element into the allocation algorithm. The minimisation factors will be:

Study siteALSFRS-R trajectory since symptom onset (a measure of functional decline that can predict individuals with fast and slow disease progression)Riluzole use

The minimisation will be hosted by the Sheffield Clinical Trial Research Unit (CTRU) randomisation system, SCRAM—a remote secure server internet-based system. Access to the allocation list will only be granted to those responsible for cleaning the data and preparing unblinded data summaries during the recruitment and follow-up. For all other members of the trial team, the allocations will be concealed until recruitment and data collection are complete.

A CTRU statistician who is not otherwise associated with the trial will generate the allocation sequence. Named persons on the delegation log, who are trained in research procedures, will allocate participants by logging into SCRAM and entering basic demographic information.

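### Allocation changed from 1:1 to 1:2, but the stated primary model omits allocation phase, so about one sixth of any unexplained between-phase difference enters the treatment effect

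*Protocol article*

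**What the plan says.** The Randomisation section of the protocol article describes the allocation ratio as "originally in a 1:1 ratio, amended during the study to a 1:2 ratio". The Sample size section places the switch, with the "first 100 participants allocated in a 1:1 ratio and the remaining participants allocated 1:2" (standard care to OptiCALS), and arrives at "a sample size of 103 in the standard care arm and 156 in the OptiCALS intervention arm, n=259 participants in total".

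The primary outcome paragraph under Data analysis then lists the model terms: "The fixed effect covariates will be time, treatment and their interaction together with variables used in the minimisation process". Centre enters as a random intercept, to be removed if the model does not converge. Time here is follow-up time, because the area between the two ALSFRS-R curves is built from the treatment and treatment-by-time coefficients.

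The minimisation factors in the Randomisation section are site, ALSFRS-R trajectory since onset, and riluzole use. Allocation phase and recruitment period appear neither there, nor in the model, nor by name among the sensitivity analyses. Secondary outcomes other than the time-to-event and rank-based ones follow the primary method, and further detail is deferred to a statistical analysis plan that is not shown.

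**The concern.** The chance of receiving OptiCALS was 1/2 in the first phase and 2/3 in the second. Randomisation therefore supports a comparison within each phase. A crude pooling of the two compares arms with different mixes of early and late participants. The plan adjusts for the variables used in allocation, but not for the one that changed the allocation probability.

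If prognosis, case mix, usual nutritional care or mode of assessment differs between early and late participants, part of that difference is attributed to treatment, in either direction. Such differences are plausible. Survival is to be reassessed 12 to 35 months after randomisation depending on recruitment date, which implies roughly 35 − 12 = 23 months of recruitment. Control care is whatever is standard at each of up to 20 sites. Assessments may be in person, by video, by telephone or self-completed.

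**Working it through.** **Arm sizes (Sample size section).** The second phase has 259 − 100 = 159 participants.
- Standard care: 50 + 159/3 = 50 + 53 = 103.
- OptiCALS: 50 + 2 × 159/3 = 50 + 106 = 156.

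Both match the stated figures. The 50:50 split of the first 100, and the switch falling at exactly 100, are taken from the plan.

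**Imbalance in phase.** First-phase share is 50/103 = 0.4854 in standard care and 50/156 = 0.3205 in OptiCALS. The gap is 0.1649, or 16.5 percentage points.

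**Bias.** Let D be the second-phase minus first-phase value of the quantity compared, after allowing for the listed covariates. Without a phase term, bias = 0.1649 × D. It favours OptiCALS if later participants do better, and standard care if they do worse.

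**Standard error implied by the stated design.** The target is "a monthly decline of 0.75 in the intervention arm vs 1.00 in the control arm", a difference of 0.25 units per month. With two-sided alpha 5% and 85% power, SE = 0.25/(1.960 + 1.036) = 0.0834 units per month. For the area, the target is 0.25 × 12²/2 = 18 unit-months, so SE = 18/2.996 = 6.0.

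**Effect of an assumed change in decline between phases.** Type I error = Φ(−1.96 + b/SE) + Φ(−1.96 − b/SE), where b is the bias. The values of D are assumptions.

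| D (units/month) | Bias | Share of 0.25 | b/SE | Type I error |
|---|---|---|---|---|
| 0.10 | 0.016 | 6.6% | 0.20 | 5.4% |
| 0.25 | 0.041 | 16.5% | 0.49 | 7.8% |
| 0.50 | 0.082 | 33% | 0.99 | 16.7% |

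At D = 0.25 with a true effect of 0.25, power moves from 85% to 93.7% or 70.6%, depending on direction.

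**Simulation check.** Data were generated from the Sample size inputs (mean 37, SD 6, AR(1) correlation 0.9, deaths scored zero, 5% withdrawal per quarter) with quarterly visits and 1,000 to 2,000 runs per setting.
- Without a phase term, slope bias was about 0.044 at D = 0.25 and 0.083 to 0.085 at D = 0.50. Type I error was about 8% and 13%.
- Area bias was 3.1 and 6.0 unit-months, against 0.0412 × 72 = 2.97 and 0.0825 × 72 = 5.94 expected. Rejection rates for the area were 7.0% and 8.7%.
- With phase and phase by time in the model, slope bias was about zero and rejection about 4% to 6%.

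The simulated standard errors were larger than those implied by 85% power (slope power about 82%, lower for the area), which reduces the inflation. The article does not give the analysis model or visit spacing behind its power, so that gap is not raised as an error. It does mean that the type I errors in the table depend on the implied SE. The size of the bias does not.

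**The case against.** Each phase is properly randomised, so drift within a phase does not bias that phase's comparison. Only about one sixth of a between-phase difference passes through. Drift carried by site, prior trajectory or riluzole use is partly adjusted for. No drift is documented: the article places the redesign for remote delivery after a delay to launch, not at participant 100. Sensitivity analyses for baseline characteristics and imbalance are promised, and the analysis plan may add the term.

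Most of this stands and limits the size of the point; it does not remove it. The covariates are listed without time interactions, so they would not absorb a change in rate of decline. The centre effect may be dropped. A check on baseline imbalance would not detect a change in usual care or in mode of assessment. The covariate list is stated, so an analysis plan that follows it would leave phase out.

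Three stronger readings are tempting, and the document does not support them.
- A reader might infer that any change over calendar time is confounded with treatment. Only unexplained differences between phases matter, and only in part.
- A reader might infer that more patients would not reduce the bias. Further 1:2 recruitment does reduce it: with 600 second-phase participants the shares would be 50/250 = 20.0% and 50/450 = 11.1%, a gap of 8.9 points.
- A reader might infer the same omission in the Cox and rank-based analyses. The article lists no covariates or strata for them and defers detail, so no error is shown there.

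**Conclusion.** The point holds in limited form. Treatment and allocation phase are associated by design, and the stated primary model does not condition on phase. The longitudinal secondary models inherit this because they follow the primary method.

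The consequence is conditional. Bias is 16.5% of whatever between-phase difference remains after the listed covariates, and zero if there is none. Over the assumed range it runs from negligible (a change in decline of 0.10 units per month) to a third of the target effect (0.50 units per month). The calculation rests on the planned switch at 100, the planned arm sizes, the assumed drift values and, for type I error, the standard error implied by 85% power. It warrants correction before unblinding but does not show that the result will be biased.

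**What to change.** Pre-specify allocation phase (1:1 v 1:2) and its interaction with follow-up time as fixed effects in the primary model, and in the longitudinal secondary models analysed in the same manner. A phase main effect alone would not remove a change in rate of decline. For consistency, stratify the Cox and rank-based analyses by phase when the analysis plan sets out their covariates. Decide this now, not after inspecting unblinded data for drift.

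Phase is known for every participant, so no new data are needed. The cost in precision is small:
- Information pooled: 103 × 156/259 = 62.04.
- Information stratified by phase: 50 × 50/100 + 53 × 106/159 = 25 + 35.33 = 60.33.
- Variance factor: 62.04/60.33 = 1.028.
- Power: Φ(0.25/(0.0834 × √1.028) − 1.96) = about 84%, against 85%. Holding 85% would need 259 × 1.0283 = 266.3, so about 267 participants.
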